The potential adverse effects of corticosteroids in pediatric shock have not been rigorously evaluated. Recent observational studies suggest that corticosteroid therapy in this population may increase hyperglycemia and secondary infections, suppress adaptive immunity, and increase mortality [23–25]. An adult RCT also suggested an increase in secondary infections and mortality with the use of corticosteroids in shock [21].

Given the poor methodological quality of the existing pediatric RCTs, the variability of administration protocols studied, contradictory results from adult trials, and the lack of information on potential adverse effects, it has been difficult to develop evidence-based guidelines for steroid use in critically ill children with fluid and vasoactive infusion dependent shock. Hydrocortisone is the most commonly used corticosteroid in large randomized controlled shock trials [21, 22] and is currently the most commonly used corticosteroid for treatment of pediatric shock [26]. However, the management of these patients remains highly variable with many critical care physicians having strongly held beliefs both for and against steroid use [27, 28].

We therefore propose a pragmatic, parallel group, randomized, placebo-controlled pilot trial of hydrocortisone for the treatment of pediatric fluid and vasoactive infusion dependent shock. The specific objectives of the STRIPES (Steroids in Fluid and Vasoactive Infusion Dependent Pediatric Shock) pilot study are to estimate the rate of patient recruitment and understand barriers to recruitment, assess the appropriateness of our eligibility criteria for a full trial, assess adherence to the treatment protocol, and assess the feasibility of collecting and shipping blood samples.

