### Interventions

Patients randomized to the hydrocortisone group will receive a 2-mg/kg hydrocortisone intravenous (IV) bolus at the time of enrollment followed by 1 mg/kg of hydrocortisone administered intravenously every 6 h (q6h) until the patient has not had an escalation in therapy (as defined by an increase in their vasoactive infusions or a fluid bolus such as normal saline, Ringer’s lactate, albumin, or any other blood product) for at least 12 h. Once these criteria are met, hydrocortisone will be reduced to 1 mg/kg every 8 h and continue at this frequency until all vasoactive infusions have been discontinued for 12 h. The weaning of hydrocortisone from q6h to q8h is important in order to ensure the patient receives the minimum amount of corticosteroid that is necessary for hemodynamic stability so as to prevent adrenal suppression and potential adverse events. If, following the initial hydrocortisone wean, the patient requires fluid boluses and/or an increase in their vasoactive infusion(s), the dosing frequency will return to every 6 h until the patient meets stability criteria again. Hydrocortisone will be continued for a maximum of 7 days to minimize the incidence of adrenal suppression. In keeping with the pragmatic nature of this trial, all other patient management, including (but not limited to) use of intubation, mechanical ventilation, sedation and analgesia, hemodynamic triggers and endpoints, red cell transfusions, antibiotics, and fluid boluses, will be left to the discretion of the treating physician. The Surviving Sepsis Campaign guidelines flowchart (see [31]) will be attached to the study protocol for easy reference by the treating physician, but its use will not be mandated; however, the use of vasoactive infusions and other therapies will be recorded.

Although we will discourage physicians from using open-label corticosteroids and carefully record any such occurrence, we will not refer to open-label use as a protocol violation so as not to deter enrollment and to encourage buy-in. In the event that the patient does not receive the full treatment as per protocol, data collection will continue.

Patients in the control group will receive a placebo consisting of normal saline equivalent in volume to the appropriate dose of hydrocortisone. The remainder of the protocol will be as per the experimental group.

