### Outcomes

This is a pilot study; hence, the primary outcome is feasibility, defined by accrual rate over 1 year. Our goal is to recruit 72 patients within this time frame. However, we will consider patient accrual to be adequate if we recruit 60 patients from seven sites within 1 year. We will also assess potential barriers to recruitment, including lack of a deferred consent model, physician- and guardian-related consent issues, availability of research personnel, and the narrow recruitment window (6 h from the initiation of vasoactive infusion). The secondary outcomes are summarized in Table 3; they include the frequency of open-label steroid use, adverse events related to corticosteroid use, time to discontinuation of vasoactive infusions, incidence of mortality, and the feasibility of blood sampling.

**Table 3 Tab3:** Secondary outcomes for the STRIPES pilot study

Outcome	Metric for analysis
Adherence to the protocol:	We will consider adherence adequate if each of goals a through c is met in 80 % of enrolled patients:
a. Time to administration of the first dose of study drug b. Weaning of drug to q8h when hemodynamically stable c. Discontinuation of drug when off all vasoactive infusions	a. Goal is <8 h from starting vasoactive medication b. Goal is to wean within 12 h of no escalation of therapy c. Goal is to discontinue between 12 and 18 h after vasoactive infusion stopped
Open-label steroid use	We will consider the number of patients started on open-label steroids to be acceptable if it occurs in <10 % of patients
Clinical outcomes:	
a. Adverse events b. Clinical endpoints	a. Severe bleeding, secondary infections, and use of insulin infusions b. Time to discontinuation of vasoactive infusion and incidence of mortality
Successful blood sampling and processing	The percentage of patients from whom blood samples are sent
	The percentage of samples sent that are successfully received and analyzed in their respective labs

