### Sample size

Based on data from our multi-center retrospective study, we expect to enroll 72 patients. This target takes into account the frequency of septic shock at each center, along with the projected consent rate at each center. This target number will: (1) allow us to assess our feasibility objectives over a reasonable time period (1 year), (2) allow each center to recruit between 6 and 24 patients, and (3) allow us to test the acceptability of our eligibility criteria as well as open-label steroid use at seven sites and with exposure to 50 different clinicians. Given that this is a pilot study, we will consider recruitment to be feasible if we achieve 80 % (60 patients) of our target enrollment, a threshold commonly used in critical care pilot studies. With 60 patients, we will have the ability to detect an adherence rate of 80 ± 10 % (meaning 80 ± 10 % of study patients will have fewer than 10 % of monitored values as violations). The median time to discontinuation of vasoactive agents observed in this pilot study will be used to better estimate the sample size needed for the full RCT.

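### Table 3 judges adherence adequate from three timing goals only, so the verdict does not depend on how many scheduled doses were given, and it does not use the adherence measure behind the stated precision

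*Protocol article*

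**What the plan says.** The Background lists among the pilot's specific objectives to "assess adherence to the treatment protocol". Table 3, in the Outcomes section, turns this into a decision rule: "We will consider adherence adequate if each of goals a through c is met in" 80 % of those enrolled.

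- Goal a: "Goal is <8 h from starting vasoactive medication".
- Goal b: "Goal is to wean within 12 h of no escalation of therapy".
- Goal c: the drug is stopped 12 to 18 h after the vasoactive infusion ends.

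The Interventions section defines the treatment more widely. After the bolus there are doses every 6 h, then every 8 h once the child is stable. If the child worsens after the wean, "the dosing frequency will return to every 6 h until the patient meets stability criteria again". Treatment lasts at most 7 days. The same section foresees incomplete treatment: "In the event that the patient does not receive the full treatment as per protocol, data collection will continue".

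The Sample size section gives another measure. It claims precision of 80 ± 10 % with 60 patients for the share of patients who have under 10 % of "monitored values as violations". It does not say what the monitored values are, and Table 3 does not refer to them.

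**The concern.** The rule is meant to judge adherence to the treatment protocol, but it looks at the start of treatment, one change of frequency and the end. What is delivered between those points does not enter it. A child with a timely first dose, wean and stop contributes a success to all three goals however many doses in between were missed, and whether or not dosing went back to every 6 h after a re-escalation.

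The Recruitment, compliance, and follow-up section expects compliance to be high. That is an assumption the pilot is well placed to test, and Table 3 cannot test it for dose delivery. The Discussion says that pilot results will be rolled into the full trial if feasibility is shown, no major protocol change is needed and the monitoring committee raises no safety concern. An adherence verdict that ignores dose delivery would inform that decision poorly.

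**Working it through.** **1. The plan's own figure.** Inputs from the Sample size section: n = 60 and p = 0.80. The 95 % level comes from the Statistical analysis section. The half-width is 1.96 × √(0.80 × 0.20 / 60) = 0.101, that is 80 ± 10.1 %. The stated precision reproduces, so the arithmetic is sound. What is unclear is which measure it applies to.

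**2. The two measures side by side.** Table 3 counts, for each of three timing goals, the share of patients who meet it. The Sample size section first computes a violation percentage within each patient and then counts patients below 10 %. With only three scored times per child, one failure is 1/3 = 33 %. A 10 % limit therefore makes sense only if more than goals a to c is monitored. The two measures are different.

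**3. Does the Table 3 verdict respond to dose delivery?** The bar is 0.80 × 60 = 48 of 60 patients for each goal. Assume that the three goals are independent and each is truly met by 90 % of patients.

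- P(at least 48 of 60 | 0.90) = 0.9943.
- All three goals: 0.9943³ = 0.983, at any level of dose delivery.

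Add a fourth, dose-level goal with the same bar, also independent:

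| True share of patients meeting the dose goal | P(at least 48 of 60) | P(adequate, four goals) |
|---|---|---|
| 90 % | 0.9943 | 0.978 |
| 80 % | 0.5764 | 0.567 |
| 70 % | 0.0568 | 0.056 |
| 50 % | about 0 | about 0 |

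With n = 72 (58 needed), the three-goal figure is 0.986, and the four-goal figures are 0.982, 0.516, 0.030 and about 0.

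**4. Where a per-patient cut-off would sit.** Illustrative course (assumed): every 6 h for 36 h, then every 8 h for 24 h. Doses after the bolus fall at 6, 12, 18, 24, 30 and 36 h, then at 44, 52 and 60 h, nine in all. Doses are missed independently with probability m (assumed).

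- Under 10 % missed: 1/9 = 11 %, so no miss is allowed, and P = (1 − m)⁹. With 10 doses due, one miss is exactly 10 % and also fails.
- At least 80 % given: 8/9 = 89 % passes and 7/9 = 78 % fails, so one miss is allowed, and P = (1 − m)⁹ + 9m(1 − m)⁸.

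| m | Under 10 % missed | At least 80 % given |
|---|---|---|
| 2 % | 0.834 (83 %) | 0.834 + 0.153 = 0.987 (99 %) |
| 5 % | 0.630 (63 %) | 0.630 + 0.299 = 0.929 (93 %) |
| 10 % | 0.387 (39 %) | 0.387 + 0.387 = 0.775 (77 %) |

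These are shares of children who meet a cut-off. They do not measure dilution of the treatment contrast: at m = 5 %, 95 % of doses are still given.

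**5. Goal c against the 7-day maximum.** Goal c allows a stop up to 18 h after the infusion ends, and 7 days − 18 h = day 6.25. If the infusion ends later than that, drug can run past day 7 and still meet goal c. From day 6.5 (7 days − 12 h) onward, a stop at day 7 comes less than 12 h after the infusion ended. In the reverse case, a child still on vasoactive infusion whose drug stops at day 7 cannot meet goal c, although the Interventions section was followed.

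**The case against.** The strongest reply is that the plan seems to envisage finer monitoring than Table 3 shows. The per-patient violation measure needs many items per child, and the list may stand in the full protocol, the case report form or the data management plan, none of which is at hand. That stands as far as the missing definition goes. It does not help the rule, because the article gives Table 3's criterion in full and limits it to three goals.

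It is also fair to say that the goals follow steps the authors single out, that adherence is secondary and descriptive, that the roll-in decision has other conditions, and that the study coordinator monitors compliance at three site visits. All of this limits the consequence. None of it makes the Table 3 verdict respond to missed doses.

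A reader might infer three stronger things that the documents do not support:

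- That a child who misses doses is classed as adherent. Table 3 tallies each goal across patients and labels no child.
- That treatment past 7 days generally passes. It usually fails goal c, unless the infusion ran beyond about day 6.25.
- That missed doses will be common, or will dilute the contrast by a known amount. The article gives no miss rate, and it cites an earlier trial at many of the same sites with only two protocol violations.

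The Sample size section's 10 % limit might seem the natural threshold for a dose goal. It would be too strict: in the nine-dose example, 95 % delivery would meet it in only 63 % of children and so fall short of the 80 % bar.

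**Conclusion.** The concern holds for the Table 3 rule. Its verdict does not depend on the share of scheduled doses given, nor on the return to 6-hourly dosing after re-escalation, and the measure behind the 80 ± 10 % precision is not the one Table 3 uses. A dose-delivery goal could change the conclusion: from 0.983 to 0.056 in the probability of an adequate verdict if that goal were truly met by 70 % of patients, but only to 0.978 if it were met by 90 %. These figures assume n = 60, independent goals and a true rate of 90 % for each timing goal.

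The 7-day maximum is a narrower matter. It escapes scoring only in long infusions, and in the reverse case it conflicts with goal c. This is a worthwhile correction to a secondary feasibility outcome. It does not affect the primary outcome.

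**What to change.** Reconcile Table 3 with the Sample size section by adding one measure to the adequacy rule: doses given divided by doses due under the Interventions section, per patient. Report the share of patients who meet a pre-specified cut-off with its 95 % confidence interval, against the same bar of 80 % of patients. Choose a cut-off that tolerates a single miss in a short course, for example at least 80 % of due doses given, and state that the 80 ± 10 % precision refers to this measure.

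Report the return to 6-hourly dosing and the 7-day maximum descriptively, among the children to whom they apply and without an adequacy threshold, since those groups may be very small. State how goal c is scored when drug is stopped at day 7 with the infusion still running, so that Table 3 and the Interventions section agree. No dosing rule changes.

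The cost is a count of doses due and given, from the dosing record that goals b and c already need, and possibly a less favourable adherence figure.

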### Sample size

Based on data from our multi-center retrospective study, we expect to enroll 72 patients. This target takes into account the frequency of septic shock at each center, along with the projected consent rate at each center. This target number will: (1) allow us to assess our feasibility objectives over a reasonable time period (1 year), (2) allow each center to recruit between 6 and 24 patients, and (3) allow us to test the acceptability of our eligibility criteria as well as open-label steroid use at seven sites and with exposure to 50 different clinicians. Given that this is a pilot study, we will consider recruitment to be feasible if we achieve 80 % (60 patients) of our target enrollment, a threshold commonly used in critical care pilot studies. With 60 patients, we will have the ability to detect an adherence rate of 80 ± 10 % (meaning 80 ± 10 % of study patients will have fewer than 10 % of monitored values as violations). The median time to discontinuation of vasoactive agents observed in this pilot study will be used to better estimate the sample size needed for the full RCT.

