### Statistical analysis

To meet the feasibility objectives of this pilot RCT, we have planned descriptive analyses. We will present recruitment rate, feasibility events, and open-label corticosteroid use as proportions with 95 % confidence intervals. Recruitment feasibility will be defined as achieving 80 % of our target goal of 72 patients. We will present continuous data as means and standard deviations, or medians and interquartile ranges, as appropriate. Patients who are randomized but withdraw or do not provide consent will be analyzed using intention to treat if they provided consent to keep their data.

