## Discussion

We recently published a systematic review [6] on the use of corticosteroids in pediatric shock. The review concluded that “The literature on the use of steroids in pediatric shock is limited in amount, methodological quality and demonstrates conflicting results. The limited evidence on which current guidelines are based strongly supports the need for a well-designed, pragmatic randomized controlled trial on the use of steroids in pediatric shock to inform future guidelines.” There are two small RCTs currently listed on www.clinicaltrials.gov (NCT01047670, NCT00732277); however, neither study has been updated since 2010. Given their size and unclear recruitment status, it is unlikely that either of the latter two trials will be able to answer the question of whether corticosteroids improve outcomes in pediatric shock.

This study is the first step towards a large RCT to provide clarity on the use of corticosteroids in critically ill children with shock. Results of the STRIPES pilot study will provide essential feasibility data for planning and conducting a larger, multi-center trial that will help to establish the role of corticosteroids in children with fluid and vasoactive infusion dependent shock. Our goal is to enroll a minimum of 60 patients at seven sites over a 1-year period. Failure to do so will prompt us to modify our plans for a future trial. If our recruitment rate is as anticipated or better, we will not modify eligibility criteria. If our recruitment rate is marginal (that is, barely achieves our goals), we will examine the number of patients excluded on the basis of each exclusion criterion, and will reconsider the necessity for any criterion that has resulted in a large number of excluded patients. We will record the number of eligible non-randomized patients and reasons for non-enrollment, and on the basis of these results, we will consider deterrents to randomization and methods to enhance enrollment of eligible patients. If the pilot study demonstrates feasibility, no major protocol changes are needed, and no safety concerns are raised by the STRIPES DMSC, then the results of the pilot study will be rolled into the full trial. However, if any of the above criteria are not met, then the protocol will be re-evaluated and the feasibility results of the pilot study published independently.

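### The primary feasibility threshold is misstated: 80 % of 72 is 57.6 (58 patients), not 60, so a final count of 58 or 59 passes one stated rule and fails the other

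*Protocol article*

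**What the plan says.** The target of 72 appears in the Abstract, Table 1, Outcomes, Sample size and Statistical analysis. The Sample size section explains its origin: "Based on data from our multi-center retrospective study, we expect to enroll 72 patients".

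The threshold for success is stated four times, in three forms:

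- **Sample size**, percentage and count treated as equal: "we will consider recruitment to be feasible if we achieve 80 % (60 patients) of our target enrollment".
- **Statistical analysis**, percentage only: "Recruitment feasibility will be defined as achieving 80 % of our target goal of 72 patients".
- **Outcomes**, count only: "we will consider patient accrual to be adequate if we recruit 60 patients from seven sites within 1 year".
- **Discussion**, count only, worded as a minimum: "Our goal is to enroll a minimum of 60 patients at seven sites over a 1-year period".

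The Discussion attaches a consequence to missing the count: "Failure to do so will prompt us to modify our plans for a future trial". It also describes an intermediate response when recruitment only just reaches the goal, namely a review of the exclusion criteria. Finally, it lists three conditions for carrying the pilot results into the full trial: feasibility shown, no need for major protocol changes, and no safety concern from the monitoring committee. No section says that 60 is a rounded figure, or which form of the threshold governs.

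**The concern.** The accrual threshold is the pass mark for the primary outcome, so it should yield one verdict for every possible count. The Sample size section equates two figures that differ. The difference is not confined to that parenthesis, because the Statistical analysis section uses the percentage without the count, and Outcomes and Discussion use the count without the percentage. An analyst working from Statistical analysis and a reader working from Outcomes would disagree at 58 or 59 patients.

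Enrolment totals are visible as they accumulate. A threshold with two readings leaves room to settle on one after the count is known, which is what fixing it in advance is meant to prevent. What depends on the verdict is whether the investigators regard their plans for the full trial as needing modification, and whether one of the conditions for using the pilot results in that trial has been met.

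**Working it through.** **Inputs.** Target 72 (Sample size and elsewhere); percentage threshold 80 % (Sample size, Statistical analysis); count threshold 60 (Outcomes, Sample size, Discussion).

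**Step 1: the plan's own figure.** The stated equivalence is that 80 % of the target equals 60.

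- 0.80 × 72 = 57.6, so the smallest whole number of patients that meets the percentage rule is 58.
- 60 / 72 = 0.833, so the count rule corresponds to 83.3 %.
- 60 / 0.80 = 75, so 60 would be 80 % of a target of 75, which is not the target in any section.

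The figure of 60 is not reproduced. Two patients would be a trivial difference in a sample size formula, but this is an exact cut-off and has to be judged on the exact product.

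**Step 2: where the rules disagree.**

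| Final count | Share of 72 | Percentage rule (at least 80 %) | Count rule (at least 60) |
|---|---|---|---|
| 57 | 79.2 % | fail | fail |
| 58 | 80.6 % | pass | fail |
| 59 | 81.9 % | pass | fail |
| 60 | 83.3 % | pass | pass |

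The conflict covers 58 and 59 and no other count.

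**Step 3: how likely that is.** The protocol gives no distribution for the total. Assume, for illustration, that it is Poisson with mean m. Then P(58 or 59) = e^(−m) × (m^58 / 58! + m^59 / 59!).

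| Assumed mean m | P(58 or 59) |
|---|---|
| 50 | 5.3 % |
| 55 | 9.3 % |
| 58 | 10.4 % |
| 60 | 10.2 % |
| 65 | 7.4 % |
| 72 (the protocol's expectation) | 2.7 % |

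**Step 4: effect on the precision statement.** The Sample size section says that 60 patients allow an adherence rate of 80 ± 10 %. The 95 % half-width is 1.96 × √(0.8 × 0.2 / n). At n = 60 this is 10.1 percentage points, and at n = 58 it is 10.3. The precision statement holds under either threshold and gives no real reason to prefer one.

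**The case against.** The strongest reply is that the intended cut-off is fairly clear. Three of the four statements name 60, and the Discussion calls it a minimum. The fourth, in Statistical analysis, repeats a percentage that the Sample size section has already rendered as 60. On that reading the threshold is 60 with a loosely stated percentage, and investigators who claimed success at 58 would contradict three explicit statements. This largely stands, and it is the reason to keep 60. It does not remove the error: the Statistical analysis section gives a complete definition without the count, and nothing in the article says that the count overrides it.

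A second reply is that the consequences at 58 or 59 are close under either rule. Under the percentage rule such a count would be a marginal pass, and the Discussion then calls for a review of the exclusion criteria. Under the count rule it is a failure that leads to modified plans. Both lead back to the design. This stands in part: the practical gap is narrower than a plain go or no-go, although the feasibility condition for using the pilot results could still come out differently.

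A reader might infer that the threshold by itself decides whether the pilot results enter the full trial. The Discussion does not support that. Feasibility is one of three conditions that must hold together, so missing the threshold can block that step, but reaching it does not secure it.

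**Conclusion.** The threshold is wrong as written. Eighty per cent of 72 is 57.6, met at 58 patients, while 60 is 83.3 %, and the sections give opposite verdicts at 58 and 59. This part is exact arithmetic and needs no assumption.

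The practical weight is small. The conflict spans two patients. Under the assumed Poisson total, the chance that it matters is about 3 % at the protocol's own expectation of 72 and about 10 % if true accrual is near 60. The higher figure applies only when accrual sits almost on the cut-off. No treatment comparison, error rate or safety procedure depends on the threshold.

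A reader might infer that the pilot has no usable success criterion, or that the investigators are free to choose one. The documents do not go that far, since most of the statements point to 60. This is a correction that should be made, not a fault that undermines the pilot.

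**What to change.** State one threshold in Outcomes, Sample size, Statistical analysis and Discussion, and do so before the final count is known. The preferable form is at least 60 patients (83 % of 72), because three of the four statements already name 60. In practice this means replacing 80 % with 83 % in Sample size and Statistical analysis, and adding the count of 60 in Statistical analysis so that the number of patients governs and not a rounded percentage. The Sample size remark that 80 % is a commonly used threshold would need rewording to match.

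The alternative, at least 58 patients (80 % of 72), is also coherent. It would mean changing the count in Outcomes, Sample size and Discussion, and it would lower the figure that most of the article uses.

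The cost of the preferred form is wording only: the stated percentage changes, and the target, design and data collection do not.

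### The ±10 % precision is stated for a different adherence measure from the one Table 3 judges, and Table 3's denominator includes children who cannot meet goals b or c

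*Protocol article*

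**What the plan says.** Under Outcomes, Table 3 sets the adequacy rule for adherence: "We will consider adherence adequate if each of goals a through c is met in 80 % of enrolled patients". The goals are:

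- a, first dose: "Goal is <8 h from starting vasoactive medication"
- b, wean: "Goal is to wean within 12 h of no escalation of therapy"
- c, stop: "Goal is to discontinue between 12 and 18 h after vasoactive infusion stopped"

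These are three separate proportions, each over everyone enrolled.

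The Sample size section then says: "With 60 patients, we will have the ability to detect an adherence rate of 80 ± 10" %. It explains the figure in brackets as "80 ± 10 % of study patients will have fewer than 10 % of monitored values as violations". That is one proportion, built from a per-patient tolerance. The article does not define the monitored values, and the tolerance does not appear in Table 3.

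The Interventions section makes the wean depend on at least 12 h without escalation and the stop on 12 h off all vasoactive infusions. It also caps treatment: "Hydrocortisone will be continued for a maximum of 7 days to minimize the incidence of adrenal suppression". The Statistical analysis section promises "recruitment rate, feasibility events, and open-label corticosteroid use as proportions with 95 % confidence intervals", and keeps patients who withdraw in the analysis if their data may be retained.

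**The concern.** There are two faults, both of definition.

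First, the criterion and its precision describe different quantities. The 80 % in Table 3 applies to each goal across patients. The 80 ± 10 % in Sample size applies to the share of patients whose own violation rate is low. Neither can be derived from the other, so a reader cannot take the ±10 % as the uncertainty around the result that will be called adequate or not.

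Second, goals b and c each need a later event that some enrolled children never have. A child still on infusions at day 7 can be treated exactly as Interventions describes and have no stop of the kind goal c scores. A child who dies on infusions cannot meet goal c either. A child who dies or is withdrawn before 12 h without escalation cannot meet goal b. All of them stay in the literal denominator.

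Assessing adherence is a named objective in the Background. The Discussion makes rolling the pilot into the full trial depend on feasibility and on no major protocol changes being needed. A shortfall caused by sick children could be read as sites not following the protocol. If the scoring is settled only after the data are seen, the choice can move the result across 80 %.

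**Working it through.** **Inputs.** n = 60, rate 80 % and half-width 10 points (Sample size); 95 % confidence (Statistical analysis); mortality 2-10 % (Background). The share of children who never reach the wean or stop point is not given. Call it f. I use f = 2-10 %, anchored on the mortality range, as an assumption.

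**1. The plan's own figure.** Half-width = 1.96 × √(p(1 − p)/n).

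- n = 60: 1.96 × √(0.80 × 0.20/60) = 0.101, or 10.1 points.
- For exactly 10 points: n = 1.96² × 0.16/0.10² = 61.5, so 62.
- Exact (Clopper-Pearson) 95 % interval for 48/60: 67.7-89.2 %.

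The ±10 % therefore reproduces, for one proportion observed in all 60 children.

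**2. What the figure is attached to.**

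| | Table 3 | Sample size |
|---|---|---|
| Unit scored | each goal | each patient |
| Number of proportions | three | one |
| Tolerance within a patient | none stated | under 10 % of monitored values |
| Adequacy threshold | 80 % for every goal | none |
| Precision stated | none | ±10 points |

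**3. Effect of the denominator if non-reachers count as not met.**

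- Rate among enrolled when the rest adhere at 80 %: 0.80 × (1 − f).
- Rate the rest must achieve to score 80 % of enrolled: 0.80/(1 − f).
- Evaluable children: 60 × (1 − f), rounded.

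| f | Evaluable of 60 | 80 % among the rest reads as | The rest must reach | Half-width at 80 % |
|---|---|---|---|---|
| 2 % | 59 | 78.4 % | 81.6 % | 10.2 points |
| 5 % | 57 | 76.0 % | 84.2 % | 10.4 points |
| 10 % | 54 | 72.0 % | 88.9 % | 10.7 points |

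In counts, an 80 % rule on 60 children allows 60 × 0.20 = 12 misses. At f = 10 %, 60 × 0.10 = 6 of those 12 are used up before any lapse by a site.

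**4. The opposite scoring.** If non-reachers count as met, the rate is 0.80 × (1 − f) + f. That is 80.4 % at f = 2 % and 82.0 % at f = 10 %. At f = 10 %, the same conduct among evaluable children reads as anything from 72 % to 82 %, depending on a rule the article does not state.

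**The case against.** **Only Table 3 sets a pass mark.** The Sample size section states a precision and no adequacy threshold. A reader might infer that the same data could pass one definition and fail the other. That does not follow, because the second has no pass mark. What stands is that the precision belongs to another measure.

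**The monitored values may not be the three goals.** If they were, under 10 % of three values would mean no violations. With each goal met in exactly 80 %, the share of children meeting all three would then lie between 3 × 0.80 − 2 = 40 % and 80 % (0.80³ = 51 % if independent). It is tempting to quote that gap, but the article does not say that the values are the goals, and a 10 % tolerance fits many values per child better. Dosing every 6 h for 7 days, for instance, would give up to 4 × 7 = 28. The full protocol may define the term. Such a definition could clarify the composite, but it would not turn it into the Table 3 criterion.

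**No rule says that non-reachers fail.** Table 3 words goals b and c conditionally, on stability and on being off infusions, so they could be scored as not applicable. That is fair. Counting them as not met is the literal reading of an enrolled denominator, not a stated rule.

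**The 7-day limit does not by itself remove goal b.** The wean needs only 12 h without escalation, so a child can meet goal b and still be on infusions at day 7. The limit bears on goal c.

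**The share of non-reachers could be set higher.** At 15 %, the rest would need 0.80/0.85 = 94 %. The article gives no support for 15 %; its only anchor is 2-10 % mortality, and not every death need precede the stop point.

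**The stakes are limited.** Adherence is a secondary, descriptive outcome, and the Discussion does not name the 80 % adherence figure as a condition for the full trial. This stands, and it keeps the point modest.

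**Conclusion.** The point holds as a defect of definition, not of arithmetic. The ±10 % is correct for one proportion in 60 children, but it is attached to a measure that does not decide adequacy. This part needs no assumption, since the article prints both definitions.

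The denominator part depends on f and on how non-reachers are scored. With f between 2 % and 10 % and non-reachers counted as not met, 80 % adherence among the rest reads as 78-72 % of enrolled, and the rest would need 82-89 % to reach the criterion. The range is only an anchor: some deaths come after the stop point, while the 7-day limit and withdrawals add children in numbers the article does not give. It fits goal c best, because fewer children should miss the wean point. The loss of precision is slight, from 10.1 to 10.7 points at n = 54. What matters is the shift in the rate set against 80 %.

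The plan should be changed here, but the primary outcome, accrual, is not affected.

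**What to change.** 1. Use the three Table 3 goals, each judged separately, as the only adherence definition in both Outcomes and Sample size. Drop the per-patient tolerance or, if it is wanted, define the monitored values and list it as an additional measure.
2. Keep all enrolled patients for goal a. Score goal b among patients who reach the protocol's wean point and goal c among those who reach its stop point. Report how many do not, with the reason (death, 7-day limit, withdrawal).
3. Replace the Sample size sentence with: *with 60 patients, an observed 80 % for a goal has a 95 % CI of about 68-89 %, slightly wider for goals b and c.*

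The cost is wording, a changed denominator for two goals, and slightly less favourable stated precision for those goals. It changes scoring only; no treatment rule, sample size or data item has to change. It should be settled before adherence data are seen by group or in total.
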